### Patient population and recruitment procedure

2.6

Participants will be recruited from Longhua Hospital affiliated to Shanghai University of Traditional Chinese Medicine. Those patients eligible for enrollment and willing to participate in the study were initially evaluated at baseline and then finally identified through a combination of clinical presentation, physical examination, imaging and laboratory tests. Considering the age of the patients enrolled in this study, the investigator must obtain the consent of the patient's immediate family besides the patient's own informed consent to start the trial. Participants will be informed about the required cooperation in the study, the potential benefits of participating in the study, the possible adverse effects, risks and discomforts of participating in the study, and the associated reimbursement costs and confidentiality of personal information. Participants will also be informed of withdrawal from this study at any time during the study and that the investigator may discontinue your participation in this study at any time out of concern for your best interests. A data collection form including all variables of interest and all potential risks will be completed by the corresponding research center. All information obtained will be kept in an e-database for future statistical analysis. Recruitment will start in January 2022 and is expected to end in December 2023. Final follow-up of all participants will be completed on December 31, 2024.

### Ethics

2.7

This study is to be conducted in accordance with the principles of the Declaration of Helsinki and has been approved by the Sichuan Regional Ethics Review Committee on Traditional Chinese Medicine. Details of the trial program have been approved by the appropriate Institutional Review Boards. Prior to the clinical trial, the participants will provide written informed consent.

### Blinding

2.8

All investigators, physicians, nurses, patients, assessors, statisticians, and participants remained blinded to group assignment until the trial ended, when all statistical analyses were finished. If any clinically significant adverse events occur after the first dose that are potentially treatment-related, the study physician will re-evaluate the participant and the PI will determine whether unblinded treatment is necessary. If non-blinding is required, the allocation information will be provided.

### Outcome measurements

2.9

#### Primary outcome measurement

2.9.1

Hemoglobin concentration is the main basis for the diagnosis of anemia and visual indicator of the patient's blood volume, therefore we consider it as an essential objective basis for assessing the efficacy of the treatment.

#### Secondary outcome measurements

2.9.2

HBL: HBL comprises a relatively high percentage of the total perioperative blood loss in ITF patients, which is the dominant cause of postoperative blood loss in intramedullary fixation systems and is strongly associated with postoperative anemia. HBL was calculated based on changes in Hct levels and estimated patient's blood volume (PBV). Following Nadler's formula, PBV (L) = k1∗height (m)^3^ + k2 ∗weight (kg) + k3. For men, k1 = 0.3669, k2 = 0.03219, and k3 = 0.6041, and for women, k1 = 0.3561, k2 = 0.03308, and k3 = 0.1833. In addition, the total red blood cell loss (TRBCL) was calculated according to the Gross formula: TRBCL (L) = PBV∗ (Hctpre − operation − Hctpost − operation), TBL(L) = TRBCL/Hctpre-operation + BVtrans. Finally, it can be derived that HBL(L) = TBL − VBL.^[13–15]^

HHS score: Anemia also interferes with postoperative joint function recovery in hip fracture patients and slows down the overall postoperative rehabilitation progress of patients16.Therefore, the Harris score was used to measure the degree of recovery of the patient's joint function after surgery, indirectly reflecting the patient's anemia. The Harris score consists of 10 questions, with 2 questions in the physician physical examination section (ROM and absence of deformity) and 8 questions in the patient-reported outcomes section.

The other outcomes also included time to get out of bed, discharge to home, 30-day readmission rates, and mortality.

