Surgery is currently recognized as the main treatment method, which can reduce pain, promote joint functional recovery, avoid many complications caused by long-term bed rest, and improve the quality of life of patients.^[4]^ Among them, the proximal femoral nail antirotation (PFNA) has the advantages of easy operation, less trauma, and stable fixation. Its characteristic is that it maintains the firm fixation and biomechanical stability of AO. The essence of BO and minimally invasive surgery is suitable for various types of femoral intertrochanteric fractures, and is currently one of the main clinical surgical methods.^[5,6]^ However, with the popularization and application of PFNA in the treatment of ITF, more and more scholars have found that although the amount of bleeding during the operation of PFNA is small, some patients show different degrees of anemia after the operation. Li analyzed the perioperative blood loss in 123 patients with ITF who underwent PFNA and found that the total blood loss from the admission day to the first and third postoperative day was 693.5 ± 359.6 mL and 863.8 ± 429.9 mL, of which the corresponding hidden blood loss was 86.8% and 89.4%, respectively.^[7]^ Tian found that 26 of 79 patients who underwent PFNA received 400 mL of blood transfusion and 22 patients received 800 mL of blood transfusion, warning the orthopedic staff to pay attention to perioperative anemia in PFNA patients.^[8]^ Postoperative anemia after fracture tends to cause ischemia and hypoxia in cells, tissues and organs, increasing the rate of blood transfusion, risk of infection, disability and mortality, triggering blood-borne diseases and affecting immune function, delaying postoperative recovery and prolonging hospitalization.^[9,10]^ Blood transfusion is the most effective way of treating anemia, which enhances hemoglobin concentration and improves anemia in a short term, but there are various severe risks such as viral infections, immune allergic reactions, acute hemolytic reactions, etc. Meanwhile, the current clinical blood use guidelines are all restrictive transfusion thresholds (hemoglobin concentration <8 g/dL).^[11]^ Other treatments include nutritional support, iron supplementation, erythropoietin, erythropoietin, and use of hemostatic drugs, and these modalities are prone to various side effects.

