### Eligibility criteria

2.3

The inclusion criteria are as follows:

1.Patients aged 60 to 85 years.2.X-ray or CT indicates ITF.3.Treated with PFNA intramedullary fixation.4.First day postoperative test results: hemoglobin concentration <8 g/dL.5.Being willing to give informed consent.^[12]^

The exclusion criteria are as follows:

1.Anemia caused by other diseases.2.Patients are with open fractures or pathological fracture caused by infection, tumor, or tuberculosis.3.Patients are with congenital hip dysplasia or osteonecrosis of the femoral head.4.Failure to understand or sign informed consent.

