### Randomization and allocation

2.5

After qualifying for screening, patients will be randomized into 2 groups with an allocation ratio of 1:1. The randomization will be created via SAS PROC PLAN software (SAS Inc., Cary, NC) by an independent third-party clinical research organization (Institute of Basic Research in Clinical Medicine, China Academy of Chinese Medical Science) and hid from the researchers by a senior data manager who is not involved in the study. The group assignment list will be sealed in light-blocking envelopes and be opened by the researchers following informed consent procedures and baseline testing.

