### Statistical analyses

2.12

A detailed statistical analysis protocol will be formulated prior to all analyses. All data will be analyzed in the clinical research center of Longhua Hospital affiliated to Shanghai University of TCM by statisticians blinded to allocation using the SPSS 20.0 statistical software (SPSS Inc., Chicago, IL). After evaluating the data distribution, 2-sample t-test (or Wilcoxon rank-sum test) will be used for the analysis of continuous variables. For categorical data, the Chi-Squared test (or Fisher exact test) will be used. Outcome variables including hemoglobin concentration, hidden blood loss, HHS scores for hip joint-specific function will be summarized with means and SDs. For statistical analysis of continuous outcomes, changes in the scores before and after treatments will be regarded as dependent variables, with the baseline scores and research institutions as covariates and the groups as fixed factors, to perform the analysis of covariance. To verify the trends for each visit in the 2 groups, repeated measures analysis of variance will be performed. For categorical outcome data, the Chi-Squared test (or Fisher exact test) will be used.^[16,17]^

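### Hidden blood loss is counted from before surgery although patients are randomised only after the day-1 haemoglobin, so loss that treatment cannot affect dilutes this secondary outcome, and no pre-treatment value is defined to remove it

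*Protocol article*

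**What the plan says.** **Definition.** Section 2.9.2 makes HBL a secondary outcome and states that "HBL was calculated based on changes in Hct levels and estimated" blood volume. Red-cell loss is "TRBCL (L) = PBV∗ (Hctpre − operation − Hctpost − operation"), which is divided by the pre-operative Hct. Transfused volume is added to give total loss, and visible loss is subtracted to give HBL. The section does not name the day of the postoperative Hct.

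**Entry and randomisation.** Section 2.3 requires "First day postoperative test results: hemoglobin concentration <8 g/dL". Section 2.5 states: "After qualifying for screening, patients will be randomized into 2 groups with an allocation ratio of 1:1". It adds that the envelopes are opened after consent and baseline testing.

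**Course of blood loss.** The only figures are in the Introduction, from a cited series of 123 patients treated with the same nail: "total blood loss from the admission day to the first and third postoperative day was 693.5 ± 359.6 mL and 863.8 ± 429.9 mL". The Introduction puts the hidden share of these totals at 86.8% by day 1 and 89.4% by day 3.

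**Analysis.** Section 2.12 lists hidden blood loss among the outcome variables. It names a two-sample t-test (or rank-sum test) for continuous variables. It also plans an ANCOVA in which "changes in the scores before and after treatments will be regarded as dependent variables", with baseline scores among the covariates, and a repeated-measures analysis over the visits. Section 2.2 schedules assessments at baseline, at days 1, 3, 7 and 14, and at months 1, 3 and 6.

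**The concern.** The outcome starts counting before surgery, while treatment can start only after the day-1 blood result. Each patient's HBL therefore contains a part fixed before allocation, and on the only figures given that part is the larger one. It adds the same expected amount to both arms together with between-patient variation, so a real effect on later loss is hard to see.

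The planned change analysis would deal with this if HBL had a pre-treatment value, but none is defined. HBL is already a change from the pre-operative state, so its pre-operative value is zero for everyone and adjusting for it removes nothing.

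A second problem arises if the formula is applied at the later visits. Recovery of Hct would then lower the calculated loss, and a group difference in red-cell recovery could be reported as a difference in bleeding.

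**Working it through.** The plan states no share or power for HBL, so there is no figure of its own to reproduce.

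**Inputs from the protocol article**
- Total loss 693.5 (SD 359.6) mL to day 1 and 863.8 (SD 429.9) mL to day 3; hidden share 86.8% and 89.4% (Introduction).
- 30 per group, one-sided α = 0.025 (section 2.11).

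**Assumed**
- SD of day-3 HBL: 384 mL (0.894 × 429.9) to 430 mL (the SD of total loss).
- Correlation r between HBL to day 1 and HBL to day 3: 0.5 to 0.9.

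**1. Share before randomisation**
- HBL to day 1: 0.868 × 693.5 = 602.0 mL.
- HBL to day 3: 0.894 × 863.8 = 772.2 mL.
- Share: 602.0 / 772.2 = 77.9%. Remainder: 170.3 mL.
- Check: visible loss is 693.5 − 602.0 = 91.5 mL at day 1 and 863.8 − 772.2 = 91.6 mL at day 3, so the added loss is all hidden and the figures agree.

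**2. How firm is 78%?** Each assumption is taken alone.
- A further 100–200 mL lost after day 3: 602.0/872.2 = 69% to 602.0/972.2 = 62%.
- 100–300 mL lost between admission and the pre-operative sample, which the formula would not count: 502.0/672.2 = 75% to 302.0/472.2 = 64%.

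**3. Power without adjustment for day 1**

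Normal approximation: power = Φ(d√(n/2) − 1.96), with √(30/2) = 3.873.
- All 170.3 mL abolished, SD 384.3: d = 0.443; Φ(1.716 − 1.96) = 40%.
- Same effect, SD 429.9: d = 0.396; Φ(1.534 − 1.96) = 34%.
- That loss halved (85.1 mL): d = 0.20–0.22; power 12–14%.
- Difference detectable with 90% power: (1.960 + 1.282) × √(2/30) = 0.837 SD, or 322 mL at SD 384. This is nearly twice the 170 mL that remains after day 1.

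**4. Power with day-1 HBL removed**

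ANCOVA residual SD = 384.3 × √(1 − r²). The SD of the day-1 to day-3 change uses 312.1 mL (0.868 × 359.6) and 384.3 mL.

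| r | ANCOVA SD | Change SD | Power, loss abolished (ANCOVA / change) | Power, loss halved (ANCOVA / change) |
|---|---|---|---|---|
| 0.5 | 333 | 354 | 51% / 46% | 17% / 15% |
| 0.7 | 274 | 278 | 67% / 66% | 22% / 22% |
| 0.8 | 231 | 231 | 82% / 82% | 30% / 30% |
| 0.9 | 168 | 171 | 98% / 97% | 50% / 49% |

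**5. Pre-operative and late values of the formula**

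HBL(t) = PBV × (Hct_pre − Hct_t)/Hct_pre + transfused volume − visible loss.
- Before surgery, Hct_t = Hct_pre and the other two terms are zero, so HBL = 0 for every patient.
- Later, each rise δ in Hct_t lowers HBL by PBV × δ/Hct_pre, although no blood already lost has been regained.

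**The case against.** **Section 2.12 may already contain the remedy.** Eligibility rests on the day-1 test and allocation is opened after baseline testing. HBL to day 1 is therefore a natural pre-treatment value, and ANCOVA on change from it would remove the untreatable part. This has force: under that reading the table in step 4 applies and the 34–40% does not. But the article does not say so. Section 2.2 lists baseline separately from postoperative day 1, the formula's own reference is pre-operative, and section 2.12 also names an unadjusted test. The stated outcome and the stated model do not fit together until the pre-treatment value is named.

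**The 78% is borrowed.** It comes from a background cohort, counts from admission, stops at day 3, and is not described as limited to patients below 8 g/dL on day 1. All of this stands, and it makes the size indicative. The order of events, with sampling before randomisation, does not depend on it.

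**Several stronger readings do not follow.**
- A reader might infer that the comparison is biased. It is not, because loss before randomisation is balanced in expectation.
- A reader might infer that 78% of the variance is noise from before treatment. It is a share of the mean. The variance explained by HBL to day 1 is r², which is 49% at r = 0.7 and 81% at r = 0.9, and r is assumed.
- A reader might take 12–14% as the power of the planned analysis. It is for an unadjusted comparison with an assumed halving of the later loss.
- A reader might say that late HBL merely repeats haemoglobin. It also contains transfused volume, visible loss and estimated blood volume. Section 2.9.2 does not state that HBL is computed late; that possibility comes from the general visit list and the repeated-measures plan.

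**Conclusion.** The point holds in a limited form. HBL as defined includes all hidden loss up to day 1, which precedes randomisation. On the background cohort this is about 78% of hidden loss to day 3, or about 62–75% under the alternative assumptions shown. The effect is dilution and added variance.

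Without day-1 adjustment, power is about 34–40% even for complete abolition of the later loss to day 3, given 30 per group and an assumed SD of 384–430 mL. A null result on HBL would therefore be weak evidence. It would not be wholly uninformative, since a large effect on later loss could still show, particularly if day-1 HBL is the covariate. A favourable result at a late visit could reflect red-cell recovery and should not be read as less bleeding.

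HBL is a secondary outcome and the trial is sized on the primary, so the main conclusion is not at risk. It is still one of the three outcome measurements that the abstract names, and worth correcting.

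**What to change.** In sections 2.9.2 and 2.12:
- Define the HBL outcome at postoperative day 3.
- Analyse it by ANCOVA with HBL to day 1, from the sample taken before the first dose, as the covariate.
- Report HBL to day 1 by group as a baseline characteristic.
- At day 7 and later, report Hct or haemoglobin and do not interpret the formula as blood loss.

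**Cost.** This is a change of wording. Days 1 and 3 are already scheduled, so no visit is added, provided Hct is measured at both.

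**Downside.** HBL then covers only the first days of a 14-day treatment, and its power stays limited: about 66–97% for complete abolition of the later loss and about 22–49% for halving it, at assumed correlations of 0.7–0.9. The report should present it as supportive.

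### Hidden blood loss is counted from before surgery although patients are randomised after the day-1 test, so loss that treatment cannot affect adds variance unless baseline is fixed at day 1

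*Protocol article*

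**What the plan says.** **Outcome.** Section 2.9.2 makes hidden blood loss (HBL) the first secondary outcome and states that "HBL was calculated based on changes in Hct levels and estimated" blood volume. Red-cell loss is defined as "TRBCL (L) = PBV∗ (Hctpre − operation − Hctpost − operation"), total loss is obtained by dividing by the preoperative hematocrit and adding transfused volume, and "Finally, it can be derived that HBL(L) = TBL − VBL". The starting point is preoperative, and no postoperative time point is named.

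**Entry and allocation.** Section 2.3 requires "First day postoperative test results: hemoglobin concentration <8 g/dL". Section 2.5 randomises patients once they have passed screening, with envelopes "opened by the researchers following informed consent procedures and baseline testing".

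**Timing of baseline.** Section 2.2 lists the assessments as baseline first, then postoperative days 1, 3, 7 and 14, then months 1, 3 and 6. Section 2.6 says that patients already eligible were first evaluated at baseline.

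**Analysis.** Section 2.12 gives a two-sample t-test (or rank-sum test) for continuous variables. It also gives an analysis of covariance in which "changes in the scores before and after treatments will be regarded as dependent variables", with baseline score and institution as covariates. HBL is among the outcome variables named there. The section does not say which HBL value is the baseline.

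**The concern.** No patient can be randomised before the day-1 hemoglobin is known. Everything lost during surgery and up to that sample is fixed before allocation, yet the HBL formula carries it into every later value. An arm comparison of cumulative HBL then measures a possibly small post-randomisation component against patient-to-patient variation that arose largely before treatment.

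Whether section 2.12 removes that variation depends on what baseline means for HBL:

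- If it is the value to day 1, change from baseline is the loss after day 1, the covariate carries information, and the analysis works.
- If it is a preoperative value, as the order of assessments in section 2.2 suggests, HBL is zero by construction. Change is then the whole cumulative loss, and the covariate is a constant that adjusts for nothing.
- The t-test, applied to the cumulative value, makes no adjustment on either reading.

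At stake is the ability of this secondary outcome to show an effect of the decoction on bleeding after day 1. The primary outcome, hemoglobin, is not touched by this point.

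**Working it through.** **Inputs from the protocol article**

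- Introduction, cited series of 123 PFNA patients: "the total blood loss from the admission day to the first and third postoperative day was" 693.5 ± 359.6 mL and 863.8 ± 429.9 mL, with hidden shares of 86.8% and 89.4%.
- Section 2.11: one-sided α = 0.025, β = 0.10, 30 per group before dropout.

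**Assumptions**

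- The article gives no SD for HBL. Scaling the day-3 SD of total loss by the hidden share gives 429.9 × 0.894 = 384 mL. The range used is 300 to 430 mL, the upper end being the unscaled SD.
- The article gives no correlation between day-1 and day-3 HBL. The range used is 0.5 to 0.9.
- Day 3 is used because it is the latest time with a loss figure. The plan does not name it for HBL.

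**Step 1: the plan's own figure.** The 30 per group cannot be reproduced, because the pretest mean and SD are not given. Inverting the two-means formula gives the standardised difference that 30 per group detects with 90% power:

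√(2/30) × (1.960 + 1.282) = 0.837 SD.

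**Step 2: how much HBL precedes allocation in the cited series**

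- To day 1: 693.5 × 0.868 = 602.0 mL
- To day 3: 863.8 × 0.894 = 772.2 mL
- Share by day 1: 602.0 / 772.2 = 0.78
- Accrued from day 1 to day 3: 772.2 − 602.0 = 170.3 mL (22%)

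**Step 3: unadjusted comparison of day-3 HBL.** Power = Φ(δ/SD × √(30/2) − 1.960).

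| Assumed SD (mL) | Difference detectable at 90% power (0.837 × SD) | Power, 170 mL abolished | Power, 170 mL halved |
|---|---|---|---|
| 300 | 251 mL | 59% | 19% |
| 384 | 322 mL | 40% | 14% |
| 430 | 360 mL | 34% | 12% |

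Example at SD 384 mL: 170.3/384.3 × 3.873 − 1.960 = −0.244, and Φ(−0.244) = 0.40. The noncentral t lowers these values by about one percentage point or less (33% at SD 430). At every SD in the range, the detectable difference exceeds the whole 170 mL.

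**Step 4: with day-1 HBL as covariate.** The residual SD is SD × √(1 − r²). When baseline is a covariate, ANCOVA gives the same treatment estimate for the change as for the final value. At SD 384 mL:

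| Correlation r | Residual SD (mL) | Power, 170 mL abolished | Power, 170 mL halved |
|---|---|---|---|
| 0.5 | 333 | 51% | 17% |
| 0.7 | 274 | 67% | 22% |
| 0.8 | 231 | 82% | 30% |
| 0.9 | 167 | 98% | 50% |

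Under the same assumptions, naming day 1 as baseline moves power for the full 170 mL from 40% to between 51% and 98%.

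**The case against.** **Section 2.12 may already do what is asked.** Section 2.6 has eligible patients evaluated at baseline, and eligibility needs the day-1 hemoglobin. Section 2.5 puts baseline testing before the envelope is opened. Section 2.12 speaks of change before and after treatment. Together these allow baseline HBL to be the day-1 value, and a preoperative baseline would give a degenerate covariate that the authors are unlikely to have intended. This stands as a permissible reading. It does not settle the matter, because section 2.2 lists baseline separately from and before day 1, and the unadjusted t-test is listed as well.

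**This may be detail for the analysis plan.** The article says that a detailed statistical protocol will follow, and leaving detail to it is no fault. But the article itself fixes the HBL formula, the timing of randomisation and the form of the analysis. The point is that these fit together on one reading of baseline and not on the other.

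**Randomisation balances the pre-dose loss.** Correct. A reader might infer that the definition hides any treatment effect, or that chance imbalance in operative loss opens a special route to a false claim. Neither follows. Pre-randomisation loss is balanced in expectation, the absolute difference is unbiased, chance imbalance is covered by the type I error of the test, and power is low rather than zero.

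**The figures are illustrative.** Also correct. The 78% is a ratio of means from a cited series that was counted from admission and is not described as restricted to hemoglobin below 8 g/dL. It is not a property of this trial. HBL might be analysed at day 7 or 14 instead. Nor is 170 mL a strict ceiling on the calculated outcome: the formula follows the hematocrit, so any recovery of red cells would lower calculated HBL further.

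**HBL is secondary.** The sample size rests on the primary outcome, so low power here contradicts nothing in section 2.11. That limits the weight of the point but does not remove a nearly free gain in precision.

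**Conclusion.** The point holds as one of precision and of an undefined baseline. HBL is anchored before surgery while allocation follows the day-1 test, so loss up to day 1 enters the outcome as variance that treatment cannot influence. In the cited series that loss is about 78% of the day-3 value. An unadjusted day-3 comparison with 30 per arm would have about 33% to 59% power for complete abolition of the remaining 170 mL, and about 11% to 19% for halving it, at SDs of 300 to 430 mL.

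These sizes rest on the assumed SD, on day 3 as the analysis time, and on a cited series that may differ from the patients enrolled here. The direction does not depend on them: adjusting for day-1 HBL gains precision whenever it correlates appreciably with the later value. The documents do not support a claim of bias, of an effect made undetectable, or of harm to the primary outcome.

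**What to change.** - **Section 2.9.2:** state that baseline HBL is HBL to the pre-dose day-1 sample. Define the efficacy outcome as HBL accrued after day 1, that is, HBL to a named early visit minus HBL to day 1.
- **Section 2.12:** analyse that outcome by ANCOVA with day-1 HBL as covariate, and state that the unadjusted t-test is not used for HBL.
- **Reporting:** give total perioperative HBL, counted from the preoperative hematocrit, descriptively by arm.

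The cost is a few sentences of wording. Day 1 is already a scheduled assessment with blood drawn for eligibility, and the hematocrit can come from that sample, so no visit or patient is added. The downside is a smaller HBL figure that is less comparable with published perioperative totals; the descriptive table keeps that comparison available.
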